### Secondary aims and objectives

The secondary aims include how to combine findings from Part A and Part B into a further optimised vaccine response to the Mpox outbreak. We also wish to understand more about how to use serological assays for other infectious diseases, and the experiences of healthcare workers and members of the public of this work.

Secondary objectives include:

Using data-linkage methods, biomedical data (geo-spatial case incidence data and antibody data) to map vaccine cold-chains for targeted vaccine deployment.Undertake exploratory immunology for insights into Mpox and other vaccine-preventable disease immunity.To conduct semi-structured interviews with healthcare professionals, project partners and members of the Rwandan public to understand their views and perspectives in taking part in a responsive clinical study for new disease outbreaks, the development of novel immunodiagnostic tools, and the vaccine cold-chain readiness to support public health measures.

The secondary endpoints of this study are

Quantitative IgG titres of other vaccine preventable diseases,Transcripts of the focus groups.A map of Rwanda’s VCC.

## Recruitment and eligibility

### Recruitment

For Part A, we will use existing operational and health data records in the Rwanda Biomedical Centre (RBC) to identify, contact and invite group-specific members of the population to consider taking part in the study.

We aim to recruit volunteers to one of the following study groups:

Group 1 (suspected exposure cohort): asymptomatic volunteers at risk of Mpox including:
Those who live within or adjacent to, or spend prolonged amounts of time in an epidemiologically identified region of Mpox transmission.Close contacts of those with microbiologically confirmed Mpox.
Group 2 (post-exposure/vaccinated cohort):
Asymptomatic volunteers who have had clinically (Table 1) or microbiologically (Table 2) confirmed Mpox infection within the last one-month (group 2a) or more than one-month ago (group 2b).Those who have received a smallpox/MVA vaccine within the last one-month (group 2c) or more than one-month ago (group 2d).
Group 3 (control cohort): asymptomatic volunteers with no known exposure to Mpox.

For Part B and the primary public health aims of the study, there will be no study volunteer recruitment or collection of personal or sensitive data. The study population here will be vaccine stock inventories in vaccine fridges. These data are already collected and available from the operational records of the Rwanda national health implementation agency, Rwanda Biomedical Centre (project partners).

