**Methods:**

This study will recruit up to 650 participants to three study groups according to Mpox exposure status and/or vaccination in Rwanda. All enrolled participants will be asked to provide demographic information, relevant medical history, up to 20mLs of venous blood and a dried blood spot capillary blood sample. For Part A of the study, samples will undergo testing for quantitative analysis of total serum antibody to Mpox specific proteins using an enzyme-linked immunosorbent assay (ELISA) and test a novel point-of-care (POC) lateral flow test to determine positive/negative qualitative serostatus. For Part B, we will collect data on VCC equipment, inventories and methods of vaccine distribution. The results of this project aim to (a) validate a blood-based ELISA assay for the detection of Mpox immunity in a target population of Rwanda, (b) generate an estimate of sero-positivity to Mpox in Rwanda, (c) evaluate the clinical performance of a novel POC lateral flow test for Mpox serostatus and (d) understand the VCC requirements for additional vaccine deployment for disease control.

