### Study interventions

#### Part A

All participants will provide informed consent using the latest Rwanda National Ethics Committee (RNEC) approved combined Study Information Booklet and Informed Consent Form (SIB/ICF) prior to commencement of any study procedures. Once informed written consent is obtained, the baseline assessments will be collected that include age, sex, region of residency, relevant medical history and national health number. A participant is enrolled at the point of sample provision. No formal follow-up of participants is planned as part of the study.

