### Sample size

#### Part A

The first stage of part A will involve validation of the University of Birmingham-developed multiplex ELISA evaluated on UK samples by University of Birmingham and UKHSA following Mpox infection with clade II virus and/or vaccination [25], using *N* = 50 samples each from groups 2b, 2d and group 3. The ELISA uses several Mpox proteins and shows excellent concordance with a multiplex bead assay developed by the UKHSA [25] on UK samples, with high sensitivity/specificity for identifying seropositivity. The performance of the ELISA will be evaluated on Rwandan participants with known status to evaluate the effect of factors such as ethnicity, nutritional status, chronic viral infection (e.g. HIV or hepatitis B) and pathogen factors such as clade Ib virus (the cause of the current outbreak) on test performance. The sub-group specific recruitment targets have therefore been expanded by 50% to accommodate potential confounders and improve the stability of estimates applied to this component of the study and the next steps in validation and assessment of clinical accuracy of novel POC LFTs. Once the performance of the Mpox ELISA is confirmed in serum, alternative sample matrices including plasma and dried blood spot (DBS) will be compared to IgG titres measured in serum in paired samples.

There is a lack of data on the current sero-prevalence of Mpox-specific immunity, which this study aims to address, meaning statistically driven power calculations are challenging. Sample sizes have been calculated according to Clinical & Laboratory Standards Institute standards and consistency with the design, setup and verification protocols used for new infectious diseases targets.

The sample size calculation has been derived from the assumption of 20% seroprevalence in the intended target-use population (high-risk individuals with no known past infection/vaccination), plus added assumptions of a 5% margin of error and a 10% allowance for the withdrawal of consent from any participants, missing data, and assay failures/invalid test results.

In total, *N* = 500 is required for this part of the study from the following study groups:

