Group 1 (suspected exposure cohort): *n* = 330.Group 2a (infection within one-month of sampling): *n* = 10.Group 2b (infection over one-month before sampling): *n* = 50.Group 2c (vaccination within one-month of sampling): *n* = 10.Group 2d (vaccination over one-month before sampling): *n* = 50.Group 3 (no known past exposure to infection or vaccination): *n* = 50.

This sample size is sufficient for stability of estimates on POC LFT performance that will be deployed in parallel to the same study volunteers at the time of sampling.

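### Group 1 pools case contacts with residents of transmission regions in no fixed share, so any single Group 1 seroprevalence depends on the recruited mix, which the 5% margin does not cover

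*Protocol article*

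**What the plan says.** The Recruitment section of the protocol article describes Group 1 as asymptomatic people at risk, with two entry routes. One is geographic: "Those who live within or adjacent to, or spend prolonged amounts of time in an epidemiologically identified region of Mpox transmission". The other is personal: "Close contacts of those with microbiologically confirmed Mpox". The inclusion criteria repeat both routes, but their geographic wording covers residence only and leaves out people who merely spend time in such a region. The exclusion criteria for Group 1 remove anyone with known exposure in the last month; contacts from before then stay eligible.

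The Sample size section (Part A) gives the group one target: "Group 1 (suspected exposure cohort): *n* = 330". The calculation rests on "the assumption of 20% seroprevalence in the intended target-use population (high-risk individuals with no known past infection/vaccination". The same sentence sets a single 5% margin of error and allows 10% for losses. Group 2, by contrast, is divided into four sub-groups by type and timing of exposure, each with its own number, two of them as small as 10.

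The abstract names as one intended result to "generate an estimate of sero-positivity to Mpox in Rwanda". The Statistical analysis plan section (Part A) calls for descriptive counts and proportions, and for predictive values of the lateral flow test against the ELISA. It does not mention entry route.

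**The concern.** Direct contact with a confirmed case and living in or next to an affected area are different levels of exposure, and there is no reason to expect equal seropositivity. If the rates differ, a pooled proportion describes no population other than the particular mix that was enrolled. Two recruitment rounds in the same communities could give different seroprevalences because the contact share changed, with no change in infection. A larger sample does not cure this: the interval narrows around a value that the mix has set.

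Two uses are at stake. The first is the seroprevalence estimate, which the abstract presents as one for Rwanda and links to models of exposure and transmission. The second is the set of predictive values for the lateral flow test, since these depend on the prevalence in the people tested. Validation of the ELISA on groups 2b, 2d and 3 is not affected.

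**Working it through.** **Inputs from the protocol article.** Group 1 size 330; assumed prevalence 20%; margin 5 points; loss allowance 10%. The confidence level is not stated, and 95% two-sided is assumed here. Prevalence by entry route is not given, so all route-specific rates below are assumptions.

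**1. The plan's own figure.** The usual normal-approximation formula gives n = 1.96² × 0.20 × 0.80 / 0.05² = 245.9, so 246. Allowing for 10% loss gives 246/0.9 = 273.3, so 274 (or 246 × 1.1 = 271). This does not reach 330. An exact (Clopper-Pearson) interval whose upper limit is no more than 5 points above 20% needs 298, which becomes 332 (298/0.9) or 328 (298 × 1.1), close to 330. By either route 330 is enough for the stated margin. After 10% loss, 297 remain, and 1.96 × √(0.16/297) = 4.5 points. The group sizes sum correctly: 330 + 10 + 50 + 10 + 50 + 50 = 500.

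**2. What that margin leaves out.** With contact share f, the pooled prevalence is f × p(contact) + (1 − f) × p(resident).

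| Assumed contacts / residents | f = 10% | f = 50% | f = 70% | Range, 10% to 70% |
|---|---|---|---|---|
| 25% / 15% | 16% | 20% | 22% | 6 points |
| 30% / 5% | 7.5% | 17.5% | 22.5% | 15 points |
| 40% / 10% | 13% | 25% | 31% | 18 points |

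The change in contact share that moves the pooled figure by a full 5 points is 5 divided by the gap in rates: 5/10 = 50 percentage points of share for the narrowest gap, 5/25 = 20 for the middle one, and 5/30 = 17 for the widest.

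**3. The planning value hides a mix.** A pooled 20% corresponds to f = (20 − p(resident)) / (p(contact) − p(resident)). That is 5/10 = 50% contacts for the first pair, 15/25 = 60% for the second and 10/30 = 33% for the third. The single 20% thus implies a contact share that the article does not state.

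**4. Predictive values.** Positive predictive value = Se × p / [Se × p + (1 − Sp) × (1 − p)], and the negative value follows likewise. Both contain p, so both inherit f when computed in Group 1.

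**5. Precision if reported by route, keeping 330 (297 evaluable, 20% assumed in each route).** The margin is 1.96 × √(0.16/m).

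- 50:50 split: m = 148, about ±6.4 points in each route.
- 25% contacts: m = 74, about ±9.1 points; residents m = 223, about ±5.3 points.
- 10% contacts: m = 30, about ±14.3 points; residents m = 267, about ±4.8 points.

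**The case against.** The best reply is that the 20% is only a planning assumption. The article never says that one pooled Group 1 proportion will be the reported result. Stratifying by route could sit in an analysis plan that is not shown, seroprevalence is not among the listed endpoints, and the sample size is also justified by lateral flow test performance. All of this is accurate, and it makes the point conditional: it bites on any single Group 1 figure. It does not remove the point. The article announces a sero-positivity estimate for Rwanda, describes the second stage of Part A as including a seroepidemiology study, and sizes Group 1 by one prevalence and one margin. The enrolled mix is also settled at recruitment and cannot be changed in analysis.

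The effect may also be small. With 25% and 15%, the pooled figure stays within 4 points of 20% even for contact shares from 10% to 90% (16% to 24%), inside the stated margin. With no gap, the mix would not matter. The last-month exclusion narrows the contact route too. These points stand, and they are why the size is given as a range.

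A reader might infer three stronger things that the documents do not support.

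- *That entry route goes unrecorded.* The baseline list ("age, sex, region of residency, relevant medical history and national health number") is introduced as what the assessments include, so it is open. Route also has to be known to judge eligibility.
- *That antibody results will be mapped to the wrong place and should be mapped by the region that qualified the person.* The secondary objective maps vaccine cold chains for deployment. It does not assign place of exposure.
- *That recruitment is by convenience.* Invitations come from existing health records. No quota or sampling scheme by route is described, but an article's silence does not show that none exists.

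**Conclusion.** The concern holds in a limited form. As described, Group 1 has no single prevalence apart from its recruited mix. A pooled seroprevalence, and predictive values computed from it, cannot be read as a property of Rwanda or of high-risk people in general, and the 5% margin does not express this uncertainty. The shift is 6 points under a 10-point gap in rates and 18 points under a 30-point gap, over contact shares of 10% to 70%. Both gaps are assumptions, since the documents give no rates by route and say that seroprevalence data are lacking. The 18 points should not be quoted as the expected effect. Nor is 330 too small: it meets the stated margin for the pooled figure at whatever mix is achieved.

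**What to change.** - Make sure that the Group 1 entry route (contact of a confirmed case, or resident of or near a transmission region) is recorded at enrolment. Bring the geographic wording in the Recruitment section and the inclusion criteria into line, so that the second category is defined in one way.
- State that Group 1 seroprevalence, and predictive values of the lateral flow test in Group 1, will be reported separately for contacts and residents.
- Give a pooled Group 1 figure only with its contact share stated, or with that share fixed in advance, and do not label it a prevalence for Rwanda.
- Keep 330, and say that the 5% margin applies to the pooled figure at its achieved mix.

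The cost is some wording, at most one enrolment field if it is not already there, and wider intervals by route: about ±6.4 points each at an even split, and about ±9.1 points for contacts if they form a quarter. Holding 5 points in each route would need about 274 recruits per route (548 in all) by the normal approximation. That is not proposed here.

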### Inclusion criteria (part A)

Healthy males and females aged between ages 5–80 years, who are able and willing to provide informed consent and will comply with the study requirements.Group 1 (suspected exposure cohort) only
Live within or adjacent to an epidemiologically identified region of Mpox transmission.Close contacts of those with microbiologically confirmed Mpox.
Group 2 (post-exposure/vaccinated cohort) only
Previous clinically or microbiologically confirmed Mpox or confirmed previous vaccination with a smallpox/MVA vaccine.Fully recovered from Mpox infection.
Group 3 (control cohort) only:
Asymptomatic with no known exposure to Mpox.

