**Fig. 1 Fig1:**
[figure not shown]
Schematic presentation of the protocol

Part A will run in two stages, the first will validate an mpox-specific ELISA developed at University of Birmingham in a Rwandan laboratory with Rwandan samples of known clinical or vaccinated mpox status. The second stage will use this ELISA once successfully validated to perform a seroepidemiology study and evaluate the performance of a lateral flow test to identify the presence of mpox-specific antibody.

For Part B we aim to understand the vaccine cold-chain (VCC) operational needs for real-world impact of Mpox vaccines deployed for disease control.

Following rapid implementation of outbreak control measures including being the first in the region to administer mpox vaccines via a ring vaccination strategy [23], case numbers in Rwanda have remained low reaching 127 as of 5th October 2025, compared to 34,000 cases in the Democratic Republic of Congo [24]. Rwanda was selected as the study setting due to its epidemiological relevance and robust public health infrastructure. Rwanda neighbours both Uganda and DRC and we expect some overlap in background infections with cross reactivity with the ELISA, and we believe this will provide data applicable to the wider region.

The availability of meticulous vaccination and infection records enables the robust selection of well-defined mpox-case, MVA-BN vaccinated, and mpox-unexposed control groups. This structured approach, paired with the representative nature of the Rwandan Vaccine Cold Chain (managed by the Rwanda Biomedical Centre, RBC), ensures the study findings are highly applicable and generalizable to other African nations facing significant Mpox outbreaks.

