### Exclusion criteria (part A)

Unwilling or unable to provide informed consent to take part.Unwilling or unable to comply with study procedures.History of any suspected or confirmed disorder of the immune system that, in the opinion of the investigators, might impair the results of the study.Have a bleeding disorder deemed significant by a member of the study team.Pregnant or breast-feeding females.Group 1 (suspected exposure cohort) only
Known history of Mpox infection.Current symptoms consistent with Mpox.Known exposure to Mpox in the last month.
Group 2 (post-exposure/vaccinated cohort) only
Participants with any ongoing symptoms of Mpox, indicating incomplete recovery.
Group 3 (control cohort only)
Symptoms of Mpox.Known exposure to Mpox in the last month.

**Table 1 Tab1:** Adapted from current WHO case definitions [23]

Clinical criteria for current or past Mpox infection
Epidemiological link to a probable or confirmed case of Mpox-21 days before symptom onset
AND
Unexplained acute rash
AND
One of the following signs or symptoms
• Headache acute onset of fever (> 38.5 °C)
• Lymphadenopathy (swollen lymph nodes)
• Myalgia (muscle pain/body aches)
• Back pain
• Asthenia (profound weakness)
AND
The following common causes of acute rash do not explain the clinical picture: varicella zoster, herpes zoster, measles, herpes simplex, bacterial skin infections, disseminated gonococcus infection, primary or secondary syphilis, chancroid, lymphogranuloma venereum, granuloma inguinale, molluscum contagiosum, allergic reaction (e.g. to plants); and any other locally relevant common causes of papular or vesicular rash.

**Table 2 Tab2:** WHO guidance for laboratory testing for hMPXV virus [24]

Microbiological criteria for current or past Mpox infection
• Nucleic acid amplification testing (NAAT) using real time or conventional hMPXV (preferable) or OPXV PCR assay on either:
o Swabs from the surface of a lesion
o Swabs from exudate from a lesion
o Roofs from more than one lesion
o Lesion crusts
• IgM detection from recent acutely ill patients
• Seroconversion of IgG in paired serum samples, collected at least 21 days apart, with the first serum sample collected during the first week of illness

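### As printed, Groups 1 and 3 overlap, so some presumed seronegative controls for the ELISA ROC may come from transmission regions, which would understate specificity and AUC

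*Protocol article*

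**What the plan says.** All references are to the protocol article.

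- **Group 1 entry** (Inclusion criteria, part A): one route is "Live within or adjacent to an epidemiologically identified region of Mpox transmission". The Recruitment section adds people who spend long periods in such a region. Close contacts of confirmed cases are a separate route.
- **Group 1 exclusions** (Exclusion criteria, part A): besides known past Mpox, "Current symptoms consistent with Mpox.Known exposure to Mpox in the last month".
- **Group 3 entry** (Inclusion criteria, part A): "Asymptomatic with no known exposure to Mpox".
- **Group 3 exclusions** (Exclusion criteria, part A): "Symptoms of Mpox.Known exposure to Mpox in the last month". Residence is not mentioned.
- **Intent** (Study design and setting): vaccination and infection records are said to allow robust selection of groups that include "mpox-unexposed control groups".
- **Use of Group 3** (Sample size, Part A; Statistical analysis plan, Part A): the first stage takes 50 samples each from Groups 2b, 2d and 3. The ROC curve contrasts presumed seropositives (infection or vaccination) with people who have neither on record, and it sets the serostatus cut-off. Under Laboratory analysis, the ELISA then becomes the reference standard for the lateral flow test.
- **Planning seroprevalence** (Sample size, Part A): "assumption of 20% seroprevalence in the intended target-use population (high-risk individuals with no known past infection/vaccination".

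**The concern.** The negative class is defined by history, not by a laboratory reference. The study's own rationale is that people without recognised disease can carry Mpox antibody. Controls from transmission regions are where such people are most likely to be found, and the printed criteria admit them.

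A truly seropositive control whom the ELISA correctly reads as positive is scored as an ELISA error. Verifying the ELISA in a Rwandan population is a primary objective, so a downward bias in its specificity and AUC affects a headline result. The overlap also leaves sites without a rule for placing a person who fits both groups.

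**Working it through.** **Step 1: do the groups overlap?** Take an asymptomatic adult who lives in a transmission region, has no known contact with a case and has no history of Mpox or vaccination.

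- Group 1: the residence criterion is met and no exclusion applies.
- Group 3: the person has no symptoms and no known exposure, and no exclusion applies.

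Could residence itself count as known exposure, and so bar the person from Group 3? No. Group 1 also excludes known exposure in the last month. If residence were known exposure, every current resident would be barred from the group that the residence criterion creates. The overlap therefore stands on the text.

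**Step 2: the plan's 20%.** This figure enters the sample size with "plus added assumptions of a 5% margin of error and a 10% allowance for the withdrawal of consent" and leads to "Group 1 (suspected exposure cohort): *n* = 330". At 95% confidence (assumed; no level is stated) the usual formula gives 1.96² × 0.20 × 0.80 / 0.05² = 246. With the 10% allowance that is 271 (× 1.1) or 274 (÷ 0.9), not 330. An exact interval with its upper limit no more than 5 points above 20% needs about 300 (60/300: 15.6% to 25.0%), and 300 × 1.1 = 330. So 330 can be reproduced that way. The group sizes add up as stated: 330 + 10 + 50 + 10 + 50 + 50 = 500. The present point does not depend on how 330 was obtained. The check shows only that 20% is a planning input.

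**Step 3: effect on apparent accuracy.** Let c be the share of controls who are truly seropositive.

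- c = (share of controls living in transmission regions) × (seroprevalence among them)
- Apparent specificity = (1 − c) × Sp + c × (1 − Se)
- Apparent AUC = (1 − c) × AUC + c × 0.5, if hidden positives share the titre distribution of the known positives

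The article gives no accuracy figures, so Se = 0.90, Sp = 0.98 and AUC = 0.97 are assumptions. The regional shares and the 5% seroprevalence below are also assumptions.

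| Scenario | c | Expected hidden positives of 50 | Apparent specificity | Apparent AUC |
|---|---|---|---|---|
| No overlap | 0 | 0 | 0.980 | 0.970 |
| Half of controls, 5% seroprevalence | 0.025 | 1.25 | 0.958 | 0.958 |
| A quarter of controls, 20% | 0.05 | 2.5 | 0.936 | 0.947 |
| Half of controls, 20% | 0.10 | 5 | 0.892 | 0.923 |
| All controls, 20% | 0.20 | 10 | 0.804 | 0.876 |

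Worked example at c = 0.10: 0.90 × 0.98 + 0.10 × 0.10 = 0.892, and 0.90 × 0.97 + 0.10 × 0.5 = 0.923. With Se = Sp = 0.95 instead, apparent specificity at c = 0.05, 0.10 and 0.20 is 0.905, 0.860 and 0.770. At c = 0.05 the chance of at least one hidden positive among 50 controls is 1 − 0.95^50 = 0.92.

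**Step 4: does the cut-off move?** Read the selection rule as maximising J = Se + Sp − 1. If hidden positives share the known positives' titre distribution, the apparent index is

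Se + (1 − c) × Sp + c × (1 − Se) − 1 = (1 − c) × (Se + Sp − 1) = (1 − c) × J.

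This is maximised at the same titre as J. A numerical check agreed: with two unit-variance normal distributions 3.29 apart, the best cut-off stayed at 1.65 for c = 0, 0.05, 0.10 and 0.20. A systematic shift needs hidden positives whose titres are distributed differently, for example lower.

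**The case against.** **The plan means the groups to be separate.** Volunteers are recruited to one group each, by group-specific invitation from records, and the controls are called unexposed. Wholesale overlap is therefore unlikely. This stands as a limit on size. It does not supply a residence rule, and infection and vaccination records cannot show sub-clinical infection. Nor is this simply detail left to a fuller document, because the group-specific criteria are printed and overlap as printed.

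**The 20% is borrowed.** A reader might take it as the expected contamination of Group 3. The documents do not support that. It is a planning figure for high-risk people, a population that on the Group 1 definition includes close contacts. The article says seroprevalence data are lacking and reports only 127 recognised Rwandan cases to 5 October 2025. At c = 0.025 the fall in specificity is about 2 points, well inside sampling error for 50 controls (49/50 has an exact 95% interval of roughly 89% to 99.9%). This objection stands.

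**Stronger readings that fail.**

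- A reader might infer from the one-month exclusion, and from the lack of a Mpox-history exclusion, that Group 3 admits people with known earlier exposure or past Mpox. It does not: the inclusion criterion has no time limit, so such a person already fails it. Only the wording is inconsistent.
- A reader might infer that the cut-off, the Group 1 seroprevalence and the lateral flow reference are necessarily distorted. Step 4 shows that a systematic shift needs a further assumption about sub-clinical titres, on which the documents give no figures.
- A reader might infer that a Group 1 versus Group 3 comparison is diluted. The Statistical analysis plan section names no such comparison.

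**Conclusion.** The overlap is real on the printed criteria, and any bias it causes runs in one direction: apparent specificity and AUC are too low. The amount cannot be fixed from the documents. Under the assumed sensitivity of 90%, specificity of 98% and AUC of 0.97, it runs from about 2 points of specificity and 0.01 of AUC at 2.5% contamination to about 18 points and 0.09 at 20%. The upper end is a bound, not an expectation. The result rests on the assumed accuracy figures, on an unknown share of controls living in transmission regions, and on an unknown seroprevalence among them. Harm to the cut-off and to later serostatus results is conditional on sub-clinical titres differing from those of known positives. The point is worth settling before the ROC analysis is run, because the remedy is cheap.

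**What to change.** 1. Add to the Group 3 exclusions anyone who meets a Group 1 criterion: living in or next to an identified transmission region, spending long periods in one, or being a close contact of a confirmed case. This makes the groups mutually exclusive.
2. For controls already enrolled, use the region of residency collected at baseline (Study interventions, Part A). Either leave overlapping controls out of the ROC negative set, or report the ROC with and without them.
3. As a wording tidy-up only, align the one-month Group 3 exclusion with the untimed inclusion criterion, and with the Sample size description of Group 3 as having no known past exposure to infection or vaccination. The Group 3 eligibility lists do not mention prior vaccination.

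The cost is eligibility wording and more targeted invitation of 50 controls. There is a small downside: controls from districts without transmission may represent the target population's background cross-reactivity less well, and the article expects such reactivity. Reporting the ROC both ways would show how much the choice of controls matters.
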